### Statistical analysis

The data will be stored and analyzed in the Radboud University Nijmegen Medical Centre using the Statistical Package for the Social Sciences (SPSS version 16.0, SPSS inc., Chicago, Illinois, USA). Data cleaning will be performed via SPSS syntax operations. All statistical tests will be done two-tailed with 95% confidence intervals.

#### Descriptive statistics

Normally distributed quantitative data will be analyzed by mean and standard deviation. Data that are not normally distributed will be reported by median and interquartile range. Qualitative data will be reported by frequency distributions and percentages.

#### Multivariate analysis

Our primary goal is to detect differences in the ESAS and HADS-scores between groups of patients with and without the telemedicine application. Because the study design involves a pretest, repeated measures and clustering, data will be analyzed with Linear Mixed Models. This method of analysis will also be used to describe our secondary outcome measures (EDIZ, NCQ, PNPC-sv, PSQ, number of hospital admission).

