### Outcome measures

#### Primary outcome

The symptom burden experienced by the patient, using the Edmonton Symptom Assessment System (ESAS) and the Hospital Anxiety and Depression Scale (HADS).

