### Sample size calculation

The null hypothesis of this cluster randomized trial is that there are no significant differences in symptom distress between palliative patients at home with and without a telemedicine-computer for videoconference. Symptom distress will be measured by the Edmonton Symptom Assessment Scale (ESAS). The ESAS is a 0 to 10 numeric scale (0 = best, 10 = worst) to rate severity of 10 symptoms. The sum of all 10 scales makes the Total Distress score (max.100). Based on a study of Follwell et al. [43] we determined a Total Distress score of 8 as the minimum clinically important difference for the power calculation. Without a cluster-effect and without repeated measures, we would need 80 patients per condition, assuming an α of .05 and a power of 80% (calculated with nQuery advisor 4.0). However, there is a cluster-effect and there are repeated measures that we corrected for.

To correct for clustering, we multiplied the abovementioned sample size with the design factor (1+(n-1)ICC), where n is the number of patients and ICC the intra cluster correlation. Assuming 3 enrolled patients per GP and an ICC of 0,1 (based on Knox & Chondros [44]), the design factor for clustering is 1,2.

To correct for repeated measures and baseline measurement, we also multiplied the sample size with the design factor ((1+(k-1)ρ)/k- ρ_0_^2^). In this formula, k is the number of repeated measures, ρ is the (mean) correlation between pairs of post-tests and ρ_0 _is the (mean) correlation between a post-test and the baseline measurement. Here, k = 13, and we state ρ = 0,45 [34] and ρ_0 _= 0,35. The design factor for repeated measures is therefore 0,37.

That makes the total required sample size 80 × 1,2 × 0,37 = 36 patients per condition. Taking into account an early drop-out of patients, we aim to include 50 patients per condition. This calculation is based on Follwell et al. [43], who considered a drop-out of 30% within an inclusion period of 1 month. Because the inclusion period in our study is longer (estimated life-expectancy of approximately 3 months at inclusion), we chose a higher drop-out percentage (39%).

Put briefly, a sample size of 100 patients (α = .05, power = 80%) is required to detect differences in change of symptom distress between the intervention group and the control group.

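### ESAS and HADS are named jointly as primary, but the null hypothesis, alpha, power and sample size cover only the ESAS Total Distress score

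*Protocol article*

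**What the plan says.** Two instruments are primary in three places of the protocol article:

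- The abstract (Methods/Design) gives symptom burden as the primary outcome, assessed weekly with ESAS and every four weeks with HADS.
- In the Primary outcome section, under Outcome measures, the entry reads: "The symptom burden experienced by the patient, using the Edmonton Symptom Assessment System (ESAS) and the Hospital Anxiety and Depression Scale (HADS").
- Statistical analysis, Multivariate analysis: "Our primary goal is to detect differences in the ESAS and HADS-scores between groups of patients with and without the telemedicine application".

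One instrument is primary in the Sample size calculation. The null hypothesis there is about symptom distress, and "Symptom distress will be measured by the Edmonton Symptom Assessment Scale (ESAS"). The effect size is also an ESAS quantity: "we determined a Total Distress score of 8 as the minimum clinically important difference for the power calculation". The starting figure is "we would need 80 patients per condition, assuming an α of .05 and a power of 80% (calculated with nQuery advisor 4.0"). HADS is not mentioned in that section.

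The level for all tests is set once, in Statistical analysis: "All statistical tests will be done two-tailed with 95% confidence intervals". The Measurement instruments section describes HADS as having an anxiety and a depression subscale. It does not say whether the total or the subscales will be compared between groups.

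**The concern.** Which outcome is primary, and which outcome the sample size serves, is core protocol content. The article gives both, and they do not agree. A reader of the outcome and analysis sections would expect a conclusion based on two instruments. A reader of the sample size section would expect one based on ESAS Total Distress.

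The practical risk is a split result. If ESAS shows no difference and HADS does, the outcome and analysis sections would allow a positive primary finding, while the null hypothesis in the sample size section would not have been rejected. The Discussion says that a positive primary result would help the adoption of telemedicine in palliative care, so the reading of such a result matters.

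**Working it through.** **Inputs from the Sample size calculation.** Unadjusted n = 80 per condition; alpha .05; power 80%; "Assuming 3 enrolled patients per GP and an ICC of 0,1"; k = 13; ρ = 0.45; ρ₀ = 0.35.

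**1. The plan's own figure.**
- Clustering factor: 1 + (3 − 1) × 0.1 = 1.2.
- Repeated-measures factor: (1 + 12 × 0.45)/13 − 0.35² = 0.4923 − 0.1225 = 0.3698.
- Patients per condition: 80 × 1.2 × 0.3698 = 35.5, rounded up to 36.

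The stated 36 reproduces. It serves one test, on ESAS, at 0.05.

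**2. Success if either score is positive.** Assume each test is two-sided at 5%. For m independent tests the chance of at least one false positive is 1 − 0.95^m:
- m = 2: 1 − 0.9025 = 0.0975.
- m = 3 (ESAS and two HADS subscales): 1 − 0.8574 = 0.1426.

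The article gives no correlation between the test statistics, so a range is shown, found by simulating correlated normal statistics with cut-off ±1.96:

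| Assumed correlation | Two tests | Three tests |
|---|---|---|
| 0 | 9.7% | 14.3% |
| 0.3 | 9.5% | 13.6% |
| 0.5 | 9.1% | 12.5% |
| 0.7 | 8.4% | 10.9% |
| 0.9 | 7.0% | 8.4% |

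Every entry exceeds 5%.

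**3. Success only if both scores are positive.** Alpha stays at or below 5%. Suppose, for illustration, that HADS also had 80% power. Joint power is then 0.80 × 0.80 = 64% at correlation 0. From the bivariate normal distribution it is 67% at 0.3, 69% at 0.5 and 71% at 0.7. It cannot exceed the lower of the two individual powers.

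**4. HADS and k = 13.** ESAS is completed weekly, which matches 13 post-tests. HADS is completed every four weeks, so about three post-tests fall in the same 13 weeks (weeks 4, 8 and 12). The factor 0.37 therefore does not apply to HADS. Its power cannot be computed, because the article gives no standard deviation, target difference or correlations for it.

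**5. Keeping two primaries with a Bonferroni split (0.025 each).** The sample size multiplier is ((2.241 + 0.842)/(1.960 + 0.842))² = 1.211. For ESAS at 80% power this gives 80 × 1.211 × 1.2 × 0.3698 = 43 evaluable patients per condition. With 36, ESAS power falls to about 72%.

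**The case against.** Several parts of the opposing case stand.

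- A journal article may leave multiplicity adjustment and testing order to a full protocol or an analysis plan that is not shown. Their absence is therefore not the point here. The point is the conflict between sections that are present. An analysis plan could add a decision rule, but the article would still name two primary instruments and state a hypothesis for one.
- The article leans towards ESAS. Besides the sample size section, the section on recruitment, consent and data collection explains the weekly ESAS by the fact that symptom burden is the primary outcome. This softens the conflict, but no section places HADS below ESAS.
- A 5% level for each score is inferred from the general statement on two-tailed tests and 95% intervals. The only alpha written out is attached to the ESAS hypothesis, and for that single test it holds.

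A reader might infer three stronger conclusions that the article does not support:

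- That alpha is certainly inflated. This needs a rule by which either score suffices. The text neither states nor excludes such a rule.
- That the error rate is at least double the stated 5%. Two tests cannot exceed 10%, and figures near that ceiling need almost independent statistics. ESAS contains depression and anxiety items, so overlap with HADS is likely. The three-test figures also assume separate subscale tests, which are not stated.
- That HADS needs 49 patients per condition. Setting k = 3 in the article's formula gives (1 + 2 × 0.45)/3 − 0.1225 = 0.511, and 80 × 1.2 × 0.511 = 49. That calculation borrows the ESAS starting n and ESAS correlations, so it is not a HADS calculation.

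**Conclusion.** The inconsistency is real. The abstract, the Primary outcome section and the Multivariate analysis section make ESAS and HADS jointly primary, while the hypothesis, alpha, power and sample size belong to ESAS Total Distress alone. For the two-instrument question, alpha of .05 and 80% power are not both secured under either success rule:

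- Either score suffices: a false-positive rate of about 7% to 10% for two tests, or about 8% to 14% with separate HADS subscale tests. Both ranges assume correlations from 0.9 to 0 and two-sided 5% per test.
- Both are required: alpha holds, but joint power is below 80%. It is about 64% to 71% for correlations from 0 to 0.7, on the generous assumption that HADS has 80% power.

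What is established is an ambiguous primary outcome with a conditional cost. An inflated alpha as such is not established.

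**What to change.** Name ESAS Total Distress as the single primary outcome, or as the first in a fixed testing order, as the Sample size calculation already implies. Make HADS secondary, or test it in a stated order only after a significant ESAS result, and say whether the total or the subscales are meant. Bring the abstract, the Primary outcome section and the Multivariate analysis section into line, together with the Primary outcome heading under Measurement instruments, where HADS also appears.

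This is a change of wording. Alpha of .05 and the ESAS-based calculation are then unaffected by this issue, and the cost is that HADS loses its equal primary status. If the sponsor prefers to keep both as primary, the success rule has to be stated and the trial re-sized for it. An equal alpha split would need 43 rather than 36 evaluable patients per condition for ESAS, and HADS would need its own difference, standard deviation and correlations.

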Due to a growing number of palliative patients and the desire for less institutionalized care, community-based palliative care will become a big challenge [18]. The development of innovative approaches to deliver good quality of care at home is therefore necessary. One such approach is the use of telemedicine. Telemedicine is the use of telecommunications and information technologies to share and maintain patient health information and to provide clinical care and health education to patients and professionals when distance separates the patients [19]. Teledermatologic consultation has been one of the first applications of telemedicine. Literature shows that this form of teleconsultation reduces the number of traditional face-to-face consultations with a dermatologist [20-23]. In addition, a telemedicine approach has also been proven cost-effective in diabetes care and pediatrics [24,25]. In the field of palliative homecare however, few quantitative studies have been carried out [26-30]. These studies often are of moderate methodological quality. Common shortcomings are small sample sizes, comparability of intervention and control groups and the handling of drop-outs [26,31].

Teleconsultation is a specialized form of telemedicine that uses technology to provide real-time visual and audio patient assessment [32]. Teleconsultation is an instrument to bring across expertise from the hospital into primary healthcare and can therefore be very useful in complex homecare for palliative patients and their families. This study aims to evaluate the effectiveness of teleconsultation in palliative homecare. The primary goal is to evaluate the effectiveness of teleconsultation on the symptom burden of palliative patients at home. Secondary objectives are 1) to investigate whether teleconsultation influences the number of hospital admissions by acting more pro-active on escalating problems of patients, 2) to consider if the burden of the family caregiver changes by giving them a better opportunity to address their needs and problems, 3) to study the patient experienced continuity of medical care in the last phase of life, 4) to assess patient and caregiver satisfaction with the teleconsultation contact and 5) to investigate patient's problems and needs for palliative care.

The objective of this report is to present the protocol of the study used for data collection in 2011 and 2012.

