### Study population

On the moment of inclusion, the patient's GP acts as the coordinator of medical care, and patients reside at their homes. Besides the place of residence, the inclusion criteria are:

- Dutch-speaking patients, aged 18 years or older, with a progressive oncological disease,

- a score of ≤ 60 on the Karnofsky Performance Scale (assessed by the GP),

- a life expectancy of ≤ 3 months.

Patients unable to give informed consent and patients with an active psychotic disorder or a serious cognitive disorder are not eligible for inclusion.

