#### Secondary outcomes

1. The number of hospital admissions, which will be obtained from the patient's file.

2. The experienced problems and needs for palliative care (PNPC-sv; Problems and Needs in Palliative Care).

3. Patient and caregiver satisfaction with the teleconsultation (PSQ; Patient Satisfaction Questionnaire).

4. The experienced continuity of medical care in the last phase of life (Nijmegen Continuity Questionnaire; NCQ).

5. The experienced burden of the family caregiver (EDIZ; self-perceived pressure from informal care).

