#### Other study outcomes

1. We will ask for some demographic information, such as age, marital status, number of children and living situation.

2. After the period of study inclusion (from the GPs patient record):

• Number of contacts by telephone with the GP practice

• Number of home visits by the GP

• Number of contacts with the GPs out of hours service

• Number of patients with complex interventions (such as palliative sedation)

• Number of and indications for hospital admissions

• Date and place of death

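### Hospital admissions, one count per patient, are assigned to a linear mixed model that ignores time at risk; the comparison misleads if observed time differs between the arms

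*Protocol article*

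**What the plan says.** The Multivariate analysis section gives its reason for the model: "Because the study design involves a pretest, repeated measures and clustering, data will be analyzed with Linear Mixed Models". It then extends the model to the secondary outcomes by name: "This method of analysis will also be used to describe our secondary outcome measures (EDIZ, NCQ, PNPC-sv, PSQ, number of hospital admission".

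The Secondary outcomes section defines this endpoint as "The number of hospital admissions, which will be obtained from the patient's file". It answers the first secondary objective in the Background: "to investigate whether teleconsultation influences the number of hospital admissions by acting more pro-active on escalating problems of patients".

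Three other places bear on time at risk:

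- Study population requires "a life expectancy of ≤ 3 months".
- Sample size calculation allows for 39% drop-out.
- Other study outcomes lists "Date and place of death" among the items taken from the GP's record, but nothing links it to the admissions analysis.

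No section says over what period admissions are counted.

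**The concern.** Of the three features that justify the linear mixed model, only clustering by GP applies to admissions. The article describes no admission count before baseline and no series of counts. The outcome is a non-negative integer, so a normal-error model is a poor default.

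Time at risk is the more important matter. Counting stops at death and, if it ends with participation, at drop-out. A linear comparison of raw counts estimates the difference in total admissions, which is rate multiplied by time observed. The objective speaks of acting early on escalating problems, which concerns how often admission is needed while the patient is alive. If one arm is observed for longer, a real reduction in rate can be hidden or a false difference shown.

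This is a model the article names, so it is not a detail left to an unseen analysis plan.

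**Working it through.** **1. The plan's own figure.** Cluster factor: 1 + (3 − 1) × 0.1 = 1.2. Repeated-measures factor: (1 + 12 × 0.45)/13 − 0.35² = 0.4923 − 0.1225 = 0.37. Then 80 × 1.2 × 0.37 = 35.5, rounded up to 36 per condition, as stated. This concerns the ESAS only. The article gives no admission rate, survival assumption or power for admissions, so all rates and survival times below are assumptions.

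**2. What the raw count estimates.** With admission rate λ and observed time T, the mean count is λ × E(T).

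- Equal λ and equal E(T): the difference is 0. Variation in T between patients within an arm does not change this.
- Equal λ = 0.2 per month, mean survival 2 vs 3 months, followed to death: 0.2 × 3 − 0.2 × 2 = +0.20 admissions per patient, with no difference in rate.
- The same with a three-month cap and exponential survival, E(T) = m(1 − e^(−3/m)): 1.55 vs 1.90 months, so 0.2 × (1.90 − 1.55) = +0.07.
- Rate halved and mean survival doubled (1.5 vs 3 months): λ × 1.5 − (λ/2) × 3 = 0. The reduction disappears.

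**3. Simulation with GP clustering.** 51 patients per arm in 17 GPs of 3, exponential survival with mean 2 months in control, between-GP frailty variance 0.1, two-sided 0.05. *Linear* is a t-test on GP totals, which equals the mixed-model arm test for balanced clusters. *Offset* is a log-rate analysis with time offset and GP-robust variance. Ranges cover 0.1 to 0.7 admissions per month, with and without extra between-patient dispersion (variance 1).

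| Scenario | Linear | Offset |
|---|---|---|
| Equal rates, equal survival: rejection | 0.04–0.05 | 0.03–0.06 |
| Equal rates, 1.5× survival, to death: rejection | 0.09–0.28 | 0.03–0.06 |
| Equal rates, 1.5× survival, 3-month cap: rejection | 0.06–0.13 | about 0.04 |
| Rate halved, intervention arm 1.5× survival, to death: power | 0.06–0.15 | 0.12–0.81 |

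Power for a halved rate with **equal** survival and no extra dispersion:

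| Rate per month | To death: linear / offset | 3-month cap: linear / offset |
|---|---|---|
| 0.1 | 0.20 / 0.18 | 0.18 / 0.16 |
| 0.2 | 0.31 / 0.34 | 0.29 / 0.28 |
| 0.35 | 0.43 / 0.52 | 0.43 / 0.45 |
| 0.7 | 0.56 / 0.78 | 0.63 / 0.71 |

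With extra dispersion the two analyses differ by at most about 0.04, in either direction.

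**4. Check under other assumptions.** 50 per arm, 13-week cap, gamma frailty, no GP clustering. Expected weeks at risk are (m/ln 2)(1 − 2^(−13/m)) for median m: 6.7, 8.2 and 9.1 weeks for medians of 6, 9 and 12. At equal rates the mean count is therefore 22% or 36% higher in the longer-lived arm.

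- Equal rates of 0.08 per week: the linear analysis rejects in 8.5% of trials (6 vs 9 weeks) and 14–15% (6 vs 12 weeks), the offset model in 5–6%.
- Rate halved from 0.10 to 0.05 per week, 6 vs 9 weeks: power 27–28% linear against 58–60% offset.

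**The case against.** **No survival difference is claimed.** The article nowhere suggests that teleconsultation prolongs life, and every inflated error rate above comes from an assumed 1.5- to 2-fold difference in survival. This stands. A reader might infer that unequal follow-up among dying patients is enough to bias the comparison. It is not: when survival has the same distribution in both arms, the linear test holds about 5%. A chance imbalance in survival still moves the estimate in the trial at hand, but the 5% already covers it.

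**Power need not be lost.** A reader might also infer that a linear model of counts always costs power. At low rates it did slightly better than the offset analysis (0.20 vs 0.18), and with overdispersed counts the two were nearly equal.

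**The offset has its own weakness.** The objective and the outcome definition speak of a number, not a rate, and dividing by survival conditions on something that happens after randomisation. The Background itself cites 30–40% of palliative patients being transferred from home to a hospital or other institution in the last week of life. Suppose each patient has a 35% chance of one admission at the end of life, the same in both arms, plus 0.02 per week beforehand, with a 13-week cap (all assumed). The offset model then shows a false benefit for the longer-lived arm:

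- Median survival 6 vs 9 weeks: it rejects in 11.8% of trials, with rate ratio 0.77, against 5.4% for the linear analysis.
- Median survival 6 vs 12 weeks: it rejects in 23–25%, with rate ratio 0.65, against 5–7%.

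This also stands, and it shapes the fix.

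**Low stakes.** The outcome is secondary, has no power target, and the model is said only to describe it. That limits the weight of the point but does not remove it. The Statistical analysis section promises two-tailed tests with confidence intervals, and an effect estimate from this model mixes rate and time whether or not it is tested.

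**Conclusion.** The point holds in a conditional form. The article names a linear mixed model for a single count per patient whose stated justification fits only in respect of clustering, and it takes no account of time at risk although death cuts follow-up short.

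- **Equal observed time in both arms:** type I error stays at about 5%. The power loss ranges from none to about 21 percentage points (0.56 vs 0.78, at 0.7 admissions per month, followed to death, no extra dispersion).
- **Observed time differs between arms**, through treatment effect, chance or drop-out: the raw count mixes rate with survival. If survival is 1.5 times longer in one arm by distribution, false rejection of equal rates is 9–28% to death or 6–13% with a three-month cap, and a halved rate in the longer-lived arm can go largely undetected.

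The article supplies no admission rate, dispersion, survival or window, so these figures show the mechanism and its range and do not predict this trial's result. The documents do not support saying that the planned analysis is biased as it stands, or that it generally loses power. The change is worth making for a named secondary objective; the primary analysis is unaffected.

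**What to change.** In Multivariate analysis, remove hospital admissions from the linear mixed model list and state instead:

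1. Admissions are analysed with a Poisson or negative binomial model that accounts for clustering by GP (random effect, or GEE with GP as cluster), with log time under observation as offset, reported as a rate ratio with 95% confidence interval.
2. The observation window is defined: when counting starts, and whether it ends at death, at the end of participation or at a fixed time. Observed time comes from the date of death already collected or the end of participation.
3. Survival is reported by arm, and the mean number of admissions per patient is estimated with the same count model without the offset, as a sensitivity analysis. If the two disagree, the reader can see whether survival or timing near death is the reason.

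The cost is a few sentences, one additional analysis, and a rate ratio in place of a mean difference. No new data are needed.
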